#### 10.3.2.3. PHASE II TRIALS – INTERIM SAFETY ANALYSIS

- An interim safety analysis will be performed based on the first ten patients included in (any of) the phase II trials.
- This analysis will be performed once data over the first cycle of treatment are available for the first 10 patients.
- Pooled data will be presented.
- Baseline patients' characteristics, treatment, and safety data (SAE and AE) will be presented over the first cycle of treatment.

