## 3.2. PHASE I – DOSE ESCALATION PART

### 3.2.1. Definitions

**Dose-limiting toxicity (DLT)** is defined as an adverse event or laboratory abnormality that fulfills all the criteria below:

- Begins on the first 28 days of treatment
- Is considered to be at least possibly related to the study treatment
- Meets one of the criteria below:
  - Hematotoxicity:
    - Persistent grade 4 neutropenia lasting  $\geq 7$  days;
    - When a neutrophil count of  $< 1000/\text{mm}^3$  and fever of  $\geq 38.0^\circ\text{C}$  is observed for  $> 2$  days;
    - Grade 4 thrombopenia or thrombopenia associated with a hemorrhage requiring platelet transfusion.
    - Grade 3 thrombocytopenia with bleeding.
  - Non-hematotoxicity:
    - $\geq$  Grade 3 non-hematotoxicities are considered as DLTs with the following specifications:
    - $\geq$  Grade 3 diarrhea, nausea, vomiting, and loss of appetite for  $\geq 5$  consecutive days (despite supportive therapy);
    - $\geq$  Grade 3 electrolyte imbalance for  $\geq 7$  consecutive days (despite supportive therapy);
    - Grade 3 dermatologic toxicity (Hand foot syndrome reaction and non-life threatening events) for  $\geq 7$  consecutive days;
    - Grade 4 dermatologic toxicity of any duration;
    - ALT/AST increases 5-8 X ULN with concomitant bilirubin increase  $< 2$  X ULN not resolving to  $< 5$  X ULN within 7 days
    - ALT/AST increases 5-8 X ULN with concomitant bilirubin increase  $> 2$  X ULN
    - ALT/AST increases  $> 8$  X ULN regardless of concomitant bilirubin increase
    - Bilirubin increase  $> 3$  X ULN not resolving to baseline within 7 days
    - $\geq$  Grade 3 immune-related adverse events lasting for  $\geq 8$  consecutive days despite steroid therapy.

In addition, the following will be considered as DLT:

- Any other study drug related AE considered significant enough to be qualified as DLT in the opinion of the investigators after discussion with the sponsor
- Any drug-related AE leading to Regorafenib or Avelumab relative dose intensity lower or equal to 75% over the first treatment cycle.

**Maximum tolerated dose (MTD):** is defined as the highest dose at which no more than 1 in 6 of the patients in the cohort experienced a DLT in the first treatment cycle.

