### 3.2.2. Treatment scheme

Regorafenib will be taken orally once daily for three weeks on/one week off, as appropriate for assigned dose level.

Avelumab will be administered intravenously, at fixed doses of 10 mg/kg, every two weeks, starting on Cycle 1 Day 15.

A treatment cycle consists of 4 weeks. Treatment may continue until disease progression or study discontinuation (withdrawal of consent, intercurrent illness, unacceptable adverse event or any other changes unacceptable for further treatment, etc.).

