### **7.3.1.Regorafenib**

Regorafenib will be taken orally on a three weeks on/one week off schedule, from Day 1 to Day 21. Regorafenib should be taken once daily at a fixed time each day. The tablets should be swallowed whole with water after a light meal that contains less than 600 calories and less than 30% fat. If a dose of Regorafenib is missed, then it should be taken on the same day as soon as the patient remembers. The patient should not take two doses on the same day to make up for a missed dose. In case of vomiting after Regorafenib administration, the patient should not take additional tablets.

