#### **Setting**

Avelumab should be administered on cycle 1 Day 15 as a 1-hour intravenous (IV) infusion, repeated every two weeks thereafter (ie. Day 1 and Day 15 of each subsequent cycle, as a 1-hour intravenous infusion). Avelumab is administered diluted with 0.9% saline solution.

Avelumab should be administered in a setting that allows for immediate access to an intensive care unit or equivalent environment and administration of therapy for anaphylaxis, such as the ability to implement immediate resuscitation measures. Steroids (dexamethasone 10 mg), epinephrine (1:1,000 dilution), allergy medications (IV antihistamines), bronchodilators, or equivalents, and oxygen should be available for immediate access.

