## 7.6. DOSING DELAYS/DOSE MODIFICATIONS AND ADVERSE EVENT MANAGEMENT

### 7.6.1. Immune related adverse events (irAE)

IrAR may be defined as an adverse event of unknown etiology, associated with drug exposure and is consistent with an immune phenomenon.

irAEs may be predicted based on the nature of the Avelumab compound, its mechanism of action, and reported experience with immunotherapies that have a similar mechanism of action. Special attention should be paid to AEs that may be suggestive of potential irAEs. An irAE can occur shortly after the first dose or several months after the last dose of treatment.

If an irAE is suspected, efforts should be made to rule out neoplastic, infectious, metabolic, toxin or other etiologic causes prior to labeling an adverse event as an irAE.

Restart Avelumab if the adverse reaction remains at Grade 1 or less. If another episode of a severe adverse reaction occurs, permanently discontinue Avelumab.

Patient requiring 2 or more consecutive cancellations of Avelumab injection should permanently discontinue avelumab. Note that further treatment by regorafenib monotherapy will be allowed until disease progression, unacceptable toxicity, etc. (see section 3.2.2 for more details).

For management, refer to the appendix 8 and to most updated Investigator Brochure.

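### The only scheduled interim phase II safety analysis stops at the end of cycle 1, after one avelumab infusion and 7 days of joint dosing, so the early look sees little of the combination

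*Protocol*

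**What the plan says.** Protocol section 10.3.2.3 states: "An interim safety analysis will be performed based on the first ten patients included in (any of) the phase II trials". The data are pooled. The analysis is done once first-cycle data are available for those ten patients, and "safety data (SAE and AE) will be presented over the first cycle of treatment".

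The dosing schedule comes from sections 3.2.2 and 7.3:

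- Cycle length: "A treatment cycle consists of 4 weeks".
- Regorafenib (7.3.1): "Regorafenib will be taken orally on a three weeks on/one week off schedule, from Day 1 to Day 21".
- Avelumab (7.3.2, Setting): "Avelumab should be administered on cycle 1 Day 15 as a 1-hour intravenous (IV) infusion, repeated every two weeks thereafter".

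On the timing of immune toxicity, section 7.6.1 says: "An irAE can occur shortly after the first dose or several months after the last dose of treatment". Sections 5.2 and 5.6 add an extended safety follow-up to 90 days after the last avelumab dose, and 5.2 gives the risk of delayed immune-related toxicity as the reason.

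The other interim analyses for phase II (10.3.2.4 and 10.3.2.5) concern efficacy only. Section 10.3.2.6 foresees no interim analysis for cohorts J to P.

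**The concern.** An early safety look at a combination should see the combination. Here the second drug arrives halfway through the reporting window. The first half of cycle 1 is regorafenib alone, and its last week is a regorafenib break. A reaction that needs a second or third avelumab infusion, or several weeks of joint exposure, falls outside the report.

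This matters because no second look is scheduled. Phase II plans 735 patients in 17 cohorts (synopsis), and recruitment mostly continues during the interim efficacy analyses (10.1.2 to 10.1.5). The ten-patient report is the one fixed point at which aggregate phase II safety data are to be set out early. A reassuring report could be taken as evidence about the combination when most of the exposure behind it is to one drug.

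**Working it through.** There is no sample size or error rate to reproduce. The check is a day count on the stated schedule, assuming full dosing without delay.

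**Inputs**
- Cycle: 28 days (3.2.2).
- Regorafenib: Days 1 to 21 of each cycle (7.3.1).
- Avelumab: Day 15 of cycle 1, then every 14 days (7.3.2).

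**Window to the end of cycle 1 (Days 1 to 28)**
- Infusions: Day 15 only. The next is Day 15 + 14 = Day 29, which is Day 1 of cycle 2 and outside the window. Count: 1.
- Joint dosing days (regorafenib days from the first infusion on): Days 15 to 21, 21 − 15 + 1 = 7.
- Observation from first avelumab: Days 15 to 28, 28 − 15 + 1 = 14 days, or 14/28 = 50% of the window.

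**Window to the end of cycle 2 (Days 1 to 56)**
- Infusions: Days 15, 29 and 43. Count: 3.
- Joint dosing days: 7 in cycle 1 plus 21 in cycle 2 (Days 29 to 49) = 28.
- Observation from first avelumab: 56 − 15 + 1 = 42 days, or 42/56 = 75% of the window.

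The cycle 1 cut thus contains 1 of the 3 infusions and 7 of the 28 joint dosing days that a two-cycle window would show.

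**What ten patients can show in either window**
- The chance of at least one case is 1 − (1 − p)^10, where p is the proportion of patients with an event inside the window. For p = 5%, 10% and 20% this gives 40%, 65% and 89%.
- With no case in ten, the one-sided 95% upper limit is 1 − 0.05^(1/10) = 25.9%.

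A longer window adds exposure to the combination. It does not make ten patients a precise sample.

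**The case against.** The strongest reply is that this is an interim table and safety is assessed fully elsewhere. That is right, and it limits the point in four ways.

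- **Other safety analyses.** A reader might infer that no other phase II safety analysis is planned, or that the combination is judged almost before it is given. The protocol does not support either reading. Section 10.3.2.2 plans a safety analysis on the safety population, which 10.2.2 defines as everyone who started either drug, with no limit by cycle. Safety profile is a secondary endpoint (9.2.2), and follow-up runs to 90 days after the last dose or to a new antitumor therapy (8.3).
- **Phase I.** A DLT must meet the condition "Begins on the first 28 days of treatment", so a reader might extend the criticism to dose finding. But the RP2D draws on safety data from all cycles (3.2.1), toxicity is tabulated by dose level and cycle (10.3.2.1), and section 7.3 already gives the phase II dose as the one defined in phase I. Nothing in phase I needs changing on this account.
- **Detection probability.** One could say that a toxicity starting in Days 29 to 56 has zero chance of appearing in the cycle 1 report. That only restates the assumed onset. It also ignores the other routes: immediate reporting of serious events (11.3), case-by-case assessment by the Vigilance Unit (11.7) and benefit/risk review by the Steering Committee (12.1.1). Section 10.3.2.3 carries no stopping rule, so no stated decision turns on the cut.
- **Restricting to avelumab recipients.** This looks like a natural remedy, but it would drop patients who stop regorafenib for toxicity before Day 15. Section 7.6.2 takes patients off study if regorafenib is permanently stopped before the first avelumab dose. Leaving them out would make the early report look too favourable and depart from the protocol's own safety population.

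What remains is the scheduling gap. An independent data monitoring committee may recommend stopping for toxicity, but it is created on request (12.1.2), and no later interim safety look is fixed. An early report does trade exposure for speed, but an update after cycle 2 would keep both.

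**Conclusion.** The point holds in a narrow form. The one scheduled interim phase II safety analysis ends when patients have had one infusion, 7 joint dosing days and 14 days of observation after first avelumab. Combination toxicity that appears later reaches the sponsor only through routine surveillance and the final cohort analyses, although the protocol anticipates late immune events.

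The schedule counts are exact if doses are given on time; delays or stops would lower them. The documents give no onset distribution for combination toxicity, so the number of events missed cannot be estimated. This is a cheap improvement of low severity. It invalidates no analysis and changes no dose or clinical rule.

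**What to change.** In section 10.3.2.3:

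- Present AE and SAE data for the first ten treated patients over the first two cycles (Days 1 to 56). Do this either in place of the cycle 1 report or as an update to it. If the cycle 1 report has already been issued, which the protocol does not say, the update is the version that applies.
- Keep every patient who initiated treatment, including those who stopped before Day 15.
- State how many of the ten received avelumab, and how many infusions each had.
- Show events before and after the first avelumab infusion separately.

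The cost is a few lines of wording and, if the report is replaced, a delay of about 4 weeks. Adverse events are already recorded throughout treatment (5.5), so no extra visit, test or patient is needed.

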#### 10.3.2.4. PHASE II TRIALS – INTERIM EFFICACY ANALYSIS (COHORTS A, B, C, D, E, F AND G)

For each cohort: interim efficacy analyses will be performed following the recruitment of the first ten patients, and every five patients thereafter (section 10.1.2).

#### 10.3.2.5. PHASE II TRIALS – INTERIM EFFICACY ANALYSIS (COHORTS H, I AND A')

For each cohort: following the two-stage optimal Simon's design, one interim efficacy analysis will be performed at the end of the 1st stage of recruitment (sections 10.1.3 to 10.1.5).

#### 10.3.2.6. PHASE II TRIALS – INTERIM EFFICACY ANALYSIS (COHORTS J TO P)

No interim analysis is foreseen.

## 11. ADVERSE EVENTS

### 11.1. DESCRIPTION OF SAFETY EVALUATION CRITERIA

The safety evaluation will comprise an evaluation of the patient's general condition (ECOG Appendix 1), a physical exam, regular blood tests and the recording of adverse events occurring throughout the study. Toxicity will be evaluated using the NCI-CTCAE scale, version 5 available on website: <http://ctep.info.nih.gov>. All appropriate treatment areas should have access to a copy of the CTCAE version 5.

In an emergency situation, the patient, his/her friends/family or treating physician will contact the investigator to report an event and/or to discuss the treatments to be implemented.

### 11.2. DEFINITION

#### 11.2.1. *Adverse event*

An adverse event is the development of an undesirable medical condition or the deterioration of a pre-existing medical condition following or during exposure to a pharmaceutical product, whether or not considered causally related to the product. An undesirable medical condition can be symptoms (eg, nausea, chest pain), signs (eg, tachycardia, enlarged liver) or the abnormal results of an investigation (eg, laboratory findings, electrocardiogram). In clinical studies, an AE can include an undesirable medical condition occurring at any time, including run-in or washout periods, even if no study treatment has been administered.

The term AE is used to include both serious and non-serious AEs.

#### 11.2.2. *Serious adverse event*

A serious adverse event is an AE occurring during any study phase (i.e., screening, run-in, treatment, wash-out, follow-up), at any dose of the study drugs that fulfils one or more of the following criteria:

- Results in death
- Is immediately life-threatening
- Requires in-patient hospitalization or prolongation of existing hospitalization
- Results in persistent or significant disability or incapacity
- Is a congenital abnormality or birth defect
- Is an important medical event that may jeopardize the patient or may require medical intervention to prevent one of the outcomes listed above.

The causality of SAEs (their relationship to all study treatment/procedures) will be assessed by the investigator(s) and communicated to Sponsor.

Any suspected transmission via a medicinal product of an infectious agent, pathogenic or non-pathogenic, is assessed as a serious adverse event with the seriousness criterion important medical event. The event may be suspected from clinical symptoms or laboratory findings indicating an infection in a patient exposed to a medicinal product. The terms "suspected transmission" and "transmission" are considered synonymous.

Any abnormal laboratory's result resulting as a grade 4 in the CTCAE version 5 will be considered as serious adverse event even if this event is not clinically relevant.

Whether or not corresponding to the above-mentioned criteria, any other adverse event considered as serious by any IMP, any healthcare professional or any investigator should be handled as a serious adverse event.

##### 11.2.2.1. DEATH

Death as such is the outcome of a SAE or the seriousness criteria and should not be used as the SAE term itself. Instead the cause of death should be recorded as the SAE term. When available, the autopsy report will be provided to the Sponsor.

##### 11.2.2.2. LIFE-THREATENING EVENT

Any event in which the patient was at risk of death at the time of the event; it does not refer to an event which hypothetically might have caused death if it were more severe.

##### 11.2.2.3. HOSPITALIZATION OR PROLONGATION OF HOSPITALIZATION

Any AE requiring hospitalization (or prolongation of hospitalization) that occurs or worsens during the course of a patient's participation in a clinical trial must be reported as a SAE. Prolongation of hospitalization is defined as any extension of an inpatient hospitalization beyond the stay anticipated/required for the initial admission, as determined by the Investigator or treating physician.

Hospitalizations that do not meet criteria for SAE reporting are:

- Reasons described in protocol [e.g., investigational medicinal product (IMP) administration, protocol-required intervention/investigations, etc]. However, events requiring hospitalizations or prolongation

of hospitalization as a result of a complication of therapy administration or clinical trial procedures will be reported as SAEs.

- Hospitalization or prolonged hospitalization for technical, practical or social reasons, in absence of an AE. However, these circumstances will be collected in the CRF.
- Pre-planned hospitalizations: Any pre-planned surgery or procedure must be documented in the source documentation and collected in the CRF. Only if the pre-planned surgery needs to be performed earlier due to a worsening of the condition, should this event (worsened condition) be reported as a SAE.

#### **11.2.3. Non serious adverse event**

A non-serious adverse event is an adverse event whose characteristics do not meet the criteria of a serious adverse event.

#### **11.2.4. Adverse effect**

An adverse effect is any untoward and unintended responses to an experimental drug regardless of the dose.

#### **11.2.5. Expected/Unexpected character**

An unexpected adverse event is an event whose nature, frequency, severity/intensity or outcome does not correspond to the information shown within the reference document for the study. The Sponsor will use as the reference safety information for the evaluation of listedness/expectedness the most updated Investigator's Brochure (IB) and/or Summary Product Characteristic (SmPC) for the studied IMP. In practice, the term "new effect" is sometimes used as a synonymous of "unexpected adverse effect".

#### **11.2.6. Intensity criterion**

It is important to distinguish between serious and severe AEs. Severity is a measure of intensity whereas seriousness is defined by the criteria in Section 11.2.2. An AE of severe intensity need not necessarily be considered serious. For example, nausea that persists for several hours may be considered severe nausea, but not a SAE. On the other hand, a stroke that results in only a limited degree of disability may be considered a mild stroke but would be a SAE.

The CTEP Active Version of the NCI Common Terminology Criteria for Adverse Event (CTCAE) will be utilized for AE reporting.

The intensity of adverse events not listed in this classification will be assessed using the following descriptors:

Mild (grade 1): does not affect the patient's usual daily activities,  
Moderate (grade 2): disturbs the patient's usual daily activities,  
Severe (grade 3): prevents the patient's usual daily activities,  
Very severe (grade 4): requires critical care/life-threatening,  
Death (grade 5).

#### **11.2.7. New information**

A new information is any new safety data that could lead to reevaluate the ratio between the benefits and risks of the research or the investigational product, to modify the use of the investigational product, the conduct of the research or the research documents or to suspend or interrupt or modify the protocol of research or similar research.

For trials of first administration or use of a health product in persons without any conditions: any serious adverse reactions. The study REGOMUNE is not concerned by this situation.

#### **11.2.8. Special considerations**

Certain product safety monitoring reports should be forwarded even if there is no associated adverse event. These reports involve circumstances that may increase the patient/consumer's risk of developing adverse events.

These circumstances include:

- medication errors,
- exposure during pregnancy,
- exposure during breastfeeding,
- overdose,
- misuse,
- occupational exposure.

Some of these special circumstances are considered in more details below.

### Overdose

There is currently no specific treatment in the event of overdose with study drug and possible symptoms of overdose are not established.

Study drug must only be used in accordance with the dosing recommendations in this protocol. Any dose or frequency of dosing that exceeds the dosing regimen specified in this protocol should be reported as an overdose.

Adverse reactions associated with overdose should be treated symptomatically and should be managed appropriately.

If an overdose drug occurs in the course of the study, the sponsor inform appropriate representatives within one day, i.e., immediately but no later than the end of the next business day of when he or she becomes aware of it.

The sponsor works with the investigator to ensure that all relevant information is provided.

For overdoses associated with SAE, standard reporting timelines apply, see Section 11.3. For other overdoses, reporting should be done within 30 days.

Medications errors: a medication error is any preventable event that may cause or lead to inappropriate medication use or patient harm while the medication is in the control of the healthcare professional, patient, or consumer. Such events may be related to professional practice, healthcare products, procedures, and systems, including: prescribing; order communication; product labeling, packaging, and nomenclature; compounding; dispensing; distribution; administration; education; monitoring; and use.

A medication error does not necessarily involve the administration of the product (e.g. the error may have been corrected prior to administration of the product).

Potential medication errors or "near-misses," which are individual reports of information or complaints about product name, labeling, or packaging similarities that do not involve a patient, are also reportable.

### Exposure during pregnancy:

Exposure during pregnancy refers to pregnancies where the fetus (from pre-embryo to birth) may have been exposed at a given time during pregnancy to a medicinal product (or a blinded treatment). Even if there is no associated adverse event, exposure during pregnancy must always be reported. It can indeed provide the opportunity to obtain pregnancy outcome important information where appropriate.

Exposure during pregnancy may occur either:

- Through maternal exposure

- \* A female becomes, or is found to be, pregnant either:

- While receiving a medicinal product
    - After discontinuing a medicinal product
    - During or following environmental exposure to a medicinal product (eg, a nurse reports she is pregnant and that she was exposed to chemotherapy drugs via inhalation or after accidentally overturning a bottle)

or

- Through paternal exposure

- \* A male has been exposed to a medicinal product (either due to treatment or environmental circumstances) prior to or around the time of conception and/or is exposed during the partner pregnancy.

Exposure during breastfeeding: exposure during breastfeeding occurs where an infant or child may have been exposed through breast milk to a medicinal product during breastfeeding by a female taking the product.

All drug exposure during breastfeeding cases are reported, whether or not there is an associated adverse event.

Occupational exposure: this refers to the exposure to a medicinal product, as a result of one's professional or non-professional occupation.

All occupational exposure to Avelumab (even if not associated with an adverse event) should be reported as an SAE.

